## Abstract

**Background:**

Depression frequently occurs in the elderly. Its cause is largely unknown, but several studies point to disturbances of biological rhythmicity. In both normal aging, and depression, the functioning of the suprachiasmatic nucleus (SCN) is impaired, as evidenced by an increased prevalence of day-night rhythm perturbations, such as sleeping disorders. Moreover, the inhibitory SCN neurons on the hypothalamus-pituitary adrenocortical axis (HPA-axis) have decreased activity and HPA-activity is enhanced, when compared to non-depressed elderly. Using bright light therapy (BLT) the SCN can be stimulated. In addition, the beneficial effects of BLT on seasonal depression are well accepted. BLT is a potentially safe, nonexpensive and well accepted treatment option. But the current literature on BLT for depression is inconclusive.

**Methods/Design:**

This study aims to show whether BLT can reduce non-seasonal major depression in elderly patients. Randomized double blind placebo controlled trial in 126 subjects of 60 years and older with a diagnosis of major depressive disorder (MDD, DSM-IV/SCID-I). Subjects are recruited through referrals of psychiatric outpatient clinics and from case finding from databases of general practitioners and old-people homes in the Amsterdam region. After inclusion subjects are randomly allocated to the active (bright blue light) vs. placebo (dim red light) condition using two Philips Bright Light Energy boxes type HF 3304 per subject, from which the light bulbs have been covered with bright blue- or dim red light- permitting filters. Patients will be stratified by use of antidepressants. Prior to treatment a one-week period without light treatment will be used. At three time points several endocrinological, psychophysiological, psychometrically, neuropsychological measures are performed: just before the start of light therapy, after completion of three weeks therapy period, and three weeks thereafter.

**Discussion:**

If BLT reduces nonseasonal depression in elderly patients, then additional lightning may easily be implemented in the homes of patients to serve as add-on treatment to antidepressants or as a stand-alone treatment in elderly depressed patients. In addition, if our data support the role of a dysfunctional biological clock in depressed elderly subjects, such a finding may guide further development of novel chronobiological oriented treatment strategies.

**Trial registration:**

ClinicalTrials.gov identifier: NCT00332670

## Background

Depression frequently occurs in the elderly. Prevalence figures of late-life depression of clinical relevance vary between 9% and 18% [1]. The effects of depressive disorders on well-being, self-sufficiency and daily functioning are enormous and and comparable to those of major chronic physical illnesses, and have clear economic consequences [1-6].

The cause of depression is unknown. However, the circadian system and a decreased activity of the suprachiasmatic nucleus (SCN), which is known as the 'biological clock' seems to be involved [7]. The age-dependent decrease of SCN activity could therefore be a risk factor for aged people to develop circadian rhythm-dependent perturbations and HPA-axis hyperactivity and depressive symptoms [8]. Disruptions in biological rhythms are known to be strongly associated with mood disorders. Indeed some of the major hallmarks of major depressive disorder (MDD) are abnormal sleep/wake, appetite, and social rhythms [9-11]. Depression symptoms are also diurnal with the most severe symptoms occurring typically in the morning [12], and depression is more prevalent in areas of the world that receive little sunlight for extended periods of time [13]. In addition, nearly all of the successful treatments for mood disorders seem to affect circadian rhythms, and it appears that the shifts, resetting and stabilization of these rhythms produced by these treatments are important for therapeutic efficacy.

### Advantages of light therapy

Patients accept and often prefer non-pharmacological treatments. The few systematic reports of side-effects suggest it is safe with only few counter indications. Light therapy also provides a viable alternative for patients who refuse, resist or cannot tolerate medication.

### Bright light therapy in Seasonal Major Depression

Bright light therapy (BLT) is considered a well and effective treatment of first choice for Seasonal Affective Disorder (SAD) [14], with an onset of action after only few days of treatment [15], and with a low side effect profile [16]. Its efficacy in SAD is comparable to that of antidepressant medication [17].

### Bright light therapy in Nonseasonal Major Depression

Trials on light therapy in nonseasonal depression have been overviewed by Kripke [18], and have been subject of three systematic reviews [17,19,20]. In short, these overviews have shown a benefit of light therapy. The Cochrane meta-analysis [19] which includes studies using light as an adjunctive treatment to antidepressants and to sleep deprivation or both, found a modest benefit of light treatment for non-seasonal depression in general, thus confirming a therapeutic benefit. An American Psychiatric Association work group concluded that efficacy appears equivalent to that of antidepressant drugs [17].

Martiny and others [21] investigated bright light compared with dim red light as adjuvant to 50 mg sertraline in a large sample (n = 90) of nonseasonal depression (mean age 45 years) and found response rates of 66,7% v. 40,7% and remission rates of 41,7% v. 14,8% for bright v. dim light, statistical significant differences favouring bright light treatment in clinical rated depression [21] scores and patient reported symptoms, and well being scales [22]. Goel and colleagues [23] gave 5 weeks morning bright light therapy (10,000 lux, 1 hour) to outpatients with chronic major depressive illness of ≥ 2 years who achieved remission rates of 50%; a control group given low-density negative air ionization showed only minor improvement.

The Committee on Chronotherapeutics [24] delegated by the International Society for Affective Disorders (SAD) concluded that light therapy hastens and potentiates the antidepressant response as an adjuvant to conventional antidepressants. Light therapy shows benefit even for patients with chronic depression of 2 years or more, outperforming their weak response to drugs. It should be noted, though, that all available reviews emphasize the need for further study because of the great diversity of short-duration study designs and relatively small sample sizes, all available overviews emphasized the need for further studies (e.g. [20,25]).

### BLT in geriatric nonseasonals

Most studies in elderly patients focussed on BLT as a therapeutic means to alleviate disruptive and cognitive symptoms of senile dementia. Recent reviews on the beneficial effects of BLT on sleep and behaviour note that the results of these studies are far from conclusive [26,27] Few empirical studies were performed in geriatric depression per se. A small crossover study (N = 10) in institutionalized patients with moderate-to-high Geriatric Depression Scale scores [28] tested morning bright (10,000 lux) versus versus dim light (300 lux), 30 minutes, 5 days, and obtained significant mood improvement under the active condition. However, these patients had no diagnosis of major depressive disorder. In the tropical climate of Taiwan, a trial of hospitalized patients with MDD (N = 30) [29] found alleviation of depressive symptoms after 5 days of morning light treatment (5000 lux, 50 minutes) in comparison with an untreated control group. However, the largest randomised controlled clinical trial in older patients (N = 81, 5 weeks) [30] found no significant benefit of bright light (10,000 lux, 1 hour; individualized according to pre-treatment phase typing into morning, midday, or evening application) over a 10-lux dim red control. Thus, results from studies on the effectiveness of BLT for geriatric depression are not conclusive.

### How light therapy may work

The neurobiological effect of light is mediated through the retina of the eye which is connected to the suprachiasmatic nuclei (SCN) situated just above the chiasmatic crossing of the optic nerve through the retinohypothalamic tract. The SCN is considered the major circadian pacemaker in mammals. Neural connections from the SCN are connected to the pineal gland and by this pathway the melatonin secretion of the pineal gland can be suppressed by light [31]. To date, the mood enhancing mechanism of bright light remains unknown.

### Wavelength

There are some indications that certain wavelengths of light are more effective than others in promoting a therapeutic response with the fewest side effects. This could be due to the ability of certain wavelengths of light to more effectively control circadian rhythms [32]. Recent studies have found that light in the blue spectrum (446–477 nm) outperforms other wavelengths in melatonin suppression, circadian phase shifting, and antidepressant effects [33,34].

### Ocular safety

Long-term follow-up of patients with cumulative exposure durations up to 1250 h demonstrated the ophthalmologic safety of light therapy, at least in patients without pre-existing ocular abnormalities [35].

### Several ways to address the placebo issue have been developed

The difficulty of creating a valid placebo condition is one of the main difficulties in light treatment trials. Eastman et al [36] and Goël et al [23] used a deactivated air ionization generator as a placebo control and checked that the daily behavioural commitment was equal to the one for light treatment and that the expectations of the patients were similar.

In SAD, Lewy et al [37] and Terman et al [38] used credible placebos by exposing the subjects to bright light at inappropriate times of the day. However, in nonseasonal depression, it appears impossible to predetermine an appropriate or inappropriate (placebo) time for light sessions as long as no single chronobiological phase alteration had been associated with depression. In the future it may well be possible to overcome this by selection of subgroups of chronobiologically homogenous patients or chronotypes. Only the Loving et al. [30] study phase-typed elderly nonseasonal depressed patients and individualized timing of light sessions according to clinical actigraphy criteria. However, the effect of light on melatonin phase appeared to be weak, suggesting low compliance or increased resistance to light in elderly patients.

### Antidepressant medication and bright light

In sum, bright light therapy might offer a safe, non-pharmacological alternative for elderly patients with a major depressive disorder. The few systematic reports of side-effects suggest it is safe with only a few counter indications. Light therapy may also provide a viable alternative for patients who refuse, resist or cannot tolerate medication. Finally, it may hasten and potentiate the antidepressant response when used as an adjuvant to conventional antidepressants. Therefore, the aims of the current study were to investigate whether bright light therapy is effective treatment in elderly outpatients suffering from a nonseasonal depressive disorder, when being used as stand-alone or as an adjuvans to antidepressive therapy.

## Methods and design

### General objectives

The purpose of this study is to investigate the following hypotheses:

1. Treatment with bright light improves mood, sleep, concentration and self-sufficiency of elderly depressed subjects. This clinical improvement is accompanied by decreases in cortisol and increase in melatonin concentrations.

2. The eventual beneficial effect of bright light treatment can be predicted by the presence of sleep-wake rhythm disturbances as found using muscle activity registration, and by cortisol and melatonin concentrations in saliva and urine over the day and the night.

### Design

A scheme-diagram of the trial protocol is presented in figure 1.

**Figure 1 F1:**
[figure not shown]
Scheme-diagram of the trial protocol.

### Participants

Volunteers are recruited in the Amsterdam region using four strategies: (1) referrals from several outpatient psychiatry secondary care settings specialized in elderly care in the Amsterdam region, (2) referrals from general practitioners, (3) advertisements in local newspapers, folders from 25 apothecaries and waiting rooms of general practitioners, (4) an active case-finding procedure by screening elderly populations from 16 General Practitioners Offices using the 15-item version of the Geriatric Depression Scale (GDS-15, [39]). Subjects with a GDS-15 score of five or more or with depressive symptoms are interviewed by telephone and/or a live interview to establish whether they fulfil the eligibility criteria.

### Inclusion and exclusion criteria

The inclusion criteria are 60 years or more of age, a primary diagnosis of Major Depressive Disorder according to DSM-IV criteria, as assessed with the Structured Clinical Interview [40] by a trained research physician (RL) or a specially trained research psychologist.

Candidates are not admitted to the study if any of the following criteria were present: (1) insufficient fluency in Dutch, (2) living outside the Amsterdam region, insufficient address for follow-up, or unwillingness to return for follow-up, (3) light treatment in the past, (4) history of light-indicated migraine or epilepsy, (5) presence of physical illnesses that require urgent specialized treatment (e.g. untreated diabetes, malignancies, chronic infections, thyroid problems, eye diseases (glaucoma, cataract) for which surgery is scheduled in near future), (6) the presence of other major axis-I disorders like bipolar disorder, dementia, delirium, all psychotic disorders, PTSD, a recent history of a suicide attempt, the presence of the DSM-IV Seasonal Pattern specifier, (7) diseases that could interfere with HPA-axis functioning, or (8) diseases or medication that could elevate the risk of light-therapy associated side effects (e.g. progressive eye diseases, senile macula degeneration, Lupus, tricyclic antidepressants, tetracyclic antibiotics), (9) current drug or alcohol abuse less than 3 months before the study, (10) any drugs (e.g. corticosteroids, cyclosporin A) known to interfere with endocrine function. Also excluded were all subjects who were taking (11) SSRIs or SNRIs shorter than 2 months.

### Interventions

We chose to use dim red light as a placebo, reasoning that because the red part of the spectrum is biologically relatively inactive, there would be no substantial effect. Another advantage of red light as placebo is that it induces very strong positive expectations quite comparable to those of bright white light [41,30].

Patients receive either early morning bright blue light or early morning dim red light. Portable light boxes are used with a fixed (non-tuneable) light-intensity (Philips Bright Light Energy^® ^boxes type HF 3304). Mistblue filters (Leevellen Lee 061) are built in to arrange the active bright-light condition. Blood-red filters (Leevellen Lee 789) are built in for the placebo dim-red light condition. On the outside of the boxes no difference is observable between the two conditions. Emitted light spectra and intensities are quantified using a lux meter at 40 cm from two light boxes. Bright light consists of approximately 10.000 lux. Dim red light consists of less than 50 lux. Environmental light in the subject's home at the designated sitting place of light therapy is measured at the start of the light therapy using a lux-meter.

We offer a 3 week treatment period of 1 hour of light therapy each day. At installation of the light devices, patients choose a 3-week-lasting fixed starting time anchored within 1 hour from their habitual wake-up time. Clock-programmable power supply of two light-boxes is set to switch 'on' at that time-point every day during the 3-week period and 'off' after one hour.

### Compliance

Compliance to light therapy is retrospectively measured by lux-meters that were built in the wrist-worn actimeters patients wear during the entire protocol. Subjects are instructed by a protocol-blinded instructor to sit at their table, with the light boxes put at a distance of approximately 40 cm from the eyes. During therapy, subjects sit at the table to have breakfast or do some reading (e.g. news paper). Participants will be asked to note their compliance in their trial-diaries.

### Sample size

Martiny et al. [21] found a moderate effect size (ES>0,50 maximum 0,66) for bright light treated group in comparison with dim light treated group on both self-assessment and observer rating scales in patients with a high prevalence of melancholic depression. Based on the literature on the expected response rate, and using conventional values for α (0.05) and β (0.80), and two-tailed tests with equal groups, the sample size aimed for in the current study is 63 patients per arm [42].

### Randomization

Randomisation was prepared by an independent researcher (BU) using a computer generated table, blocking in subsets of 10, transcribed to closed envelope messages. Stratification is applied for use antidepressant medication (SSRIs and SRNIs were allowed). After inclusion the researcher sends an email with name, contact information and condition i.e. AD+ or AD-) to one of our two specially trained protocol-blinded instructors. As a check the instructor writes the allocated condition onto a paper which is kept in a special envelope in the same box with the closed envelopes.

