### Statistical analysis

Data will be analyzed using SPSS 16.0. Analyses are performed using intention-to-treat principles. Therefore, drop-outs are distinguished into 'drop-outs before T1 assessment' and 'drop-outs after T1 assessment'. When only a randomisation assessment (T0) is available, subjects are considered lost to follow-up. For 'drop-outs after T1 assessment' the principle of LOCF (last observation carried forward) will be used. For sensitivity analysis, the more conservative LOCF variant will be calculated where T0-data will be carried forward, and a completers analysis will be performed.

Baseline characteristics across the treatment groups are compared using analysis of variance (ANOVA) and χ^2^-statistics.

As the primary analysis efficacy of treatment is tested by performing a repeated measures analysis of variance (RMANOVA) on HADRS-17 scores at T0, T1 and T2. To control for possible difference in baseline severity scores baseline values for HADRS-17 are used as covariates. Repeated contrasts are applied to compare effects in the treatment period with effects after the treatment period. As secondary analyses efficacy of treatment is tested by performing RMANOVA on the other depression symptom scales (SIGH-SAD scores, HAM-D6, MADRS-scores). As tertiary analyses depression outcome measures are dichotomised to responders and non-responders, where response is defined as a decrease of ≥ 50% on the HADRS-17, HAM-D6, SIGH-SAD and MADRS scales. Responder rates will also be presented as odd's ratios and NNT's.

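### The stated primary model omits the antidepressant stratum used in randomisation; adding it is nearly free, and claims for each use need per-stratum estimates

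*Protocol article*

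**What the plan says.** Antidepressant use is the only stratification factor named. The abstract (Methods/Design) states "Patients will be stratified by use of antidepressants", and the Randomization section repeats it: "Stratification is applied for use antidepressant medication (SSRIs and SRNIs were allowed". The same section describes "blocking in subsets of 10".

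Statistical analysis sets the primary test as a "repeated measures analysis of variance (RMANOVA) on HADRS-17 scores at T0, T1 and T2". Its adjustment is stated as follows: "To control for possible difference in baseline severity scores baseline values for HADRS-17 are used as covariates". The secondary tier applies the same method to the other depression scales. The tertiary tier dichotomises the scales into response and reports odds ratios and numbers needed to treat. Antidepressant use appears in none of the three tiers, whether as a factor, as an interaction or as a subgroup.

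Two places refer to both ways of using the treatment. The aim at the end of the Background asks whether bright light is effective "when being used as stand-alone or as an adjuvans to antidepressive therapy". The abstract's Discussion says that, if the treatment works, extra lighting could be put in patients' homes "to serve as add-on treatment to antidepressants or as a stand-alone treatment in elderly depressed patients".

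**The concern.** Two things follow from the mismatch between randomisation and model.

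The first is precision. Stratified allocation balances antidepressant users across the arms, so differences between users and non-users add almost nothing to the true variability of the arm difference. A model without the stratum still counts those differences as error. If they exist beyond what baseline severity explains, the reported interval is wider than it need be and the test is conservative.

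The second is interpretation. The stated analysis gives one effect averaged over users and non-users. The aim and the closing remark of the abstract speak of two uses. A positive average could come mainly from one stratum, and nothing in the stated analyses would show this.

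**Working it through.** **The plan's own figure.** Sample size gives 63 per arm, two-sided alpha 0.05, 0.80 (printed as β, read as power) and an effect size above 0.50. With d = 0.50, n per arm = 2 × (1.96 + 0.8416)² / 0.5² = 62.8, so 63. This reproduces the target as a single pooled comparison of two arms.

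**Inputs.** From the document: 63 per arm, alpha 0.05, d = 0.50, blocks of 10. Not in the document, so assumed and shown as ranges: R², the share of outcome variance left after baseline adjustment that antidepressant use explains; and the share of patients on antidepressants. Blocks are taken to be formed within strata. The SD unit is that of the model error without the stratum.

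**Cost of leaving out the stratum.** The model SE is √(2/63) = 0.178 SD. The true SE under stratified allocation is 0.178 × √(1 − R²).

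- SE too wide by the factor 1/√(1 − R²).
- True alpha = 2 × [1 − Φ(1.96/√(1 − R²))].
- Power without the stratum = Φ[(0.5 − 1.96 × 0.178) / (0.178 × √(1 − R²))].
- Power with the stratum = Φ[0.5 / (0.178 × √(1 − R²)) − 1.96].

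| Assumed R² | SE too wide | True alpha | Power without v. with |
|---|---|---|---|
| 0 | 0% | 0.050 | 80.1 v. 80.1% |
| 0.05 | 2.6% | 0.044 | 80.7 v. 82.1% |
| 0.10 | 5.4% | 0.039 | 81.4 v. 84.1% |

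To express the power gap in patients, find the total N at which the adjusted model has the power of the unadjusted one. For R² = 0.05, power 80.74% corresponds to z = 0.868, so n per arm = 2 × 0.95 × ((1.96 + 0.868)/0.5)² = 60.8. The total is 121.6, about 4 fewer than 126. For R² = 0.10, z = 0.892 gives 2 × 0.90 × (2.852/0.5)² = 58.6 per arm, 117.1 in total, about 9 fewer.

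**Simulation check.** Stratified permuted blocks of 10, N = 126, even strata, 8,000 runs per setting. At R² = 0.10 the mean model SE was 0.178 without and 0.169 with the stratum, type I error 0.038 v. 0.049, and power 80.8 v. 83.6%. At R² = 0 both models behaved alike (type I error 0.048 v. 0.047, power 79.9% for both).

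**Does a repeated-measures model remove the problem?** A stratum shift that is constant over T0, T1 and T2 cancels in time-by-arm contrasts. But baseline is both the T0 value and the covariate, so nothing is left at T0 after adjustment. A stratum effect remaining at T1 is then, in the T0-to-T1 contrast, a stratum-by-time effect, and it does not cancel. In the T1-to-T2 contrast an effect of equal size at both visits does cancel.

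**Precision for each use.** At an assumed even split there are 31.5 per arm in each stratum.

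- Power at d = 0.5: Φ(0.5/√(2/31.5) − 1.96) = Φ(0.024), about 51%. The 95% half-width is 1.96 × 0.252 = 0.49 SD.
- Interaction: SE = √(4/31.5) = 0.356. Power for a 0.5 SD difference between strata is Φ(0.5/0.356 − 1.96), about 29%. The half-width is 0.70 SD.
- If a stratum holds 20% to 80% of patients, its power runs from 24% to 71% and its half-width from 0.78 to 0.39 SD.

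**The case against.** Only a journal article is at hand, and articles often leave model factors and subgroup tables to the full protocol or analysis plan. The text does not say that baseline is the sole covariate, and nothing in it rules the stratum out. This stands as a reason for modesty: the finding is an omission from a stated model, not a contradiction. It does not dispose of the point, because the article sets out the model, a covariate, the contrasts, three tiers and the missing-data rules, and the only named design factor is absent from all of them.

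A reader might infer that the planned errors are too wide as a matter of fact. The document does not support that. At R² = 0 there is no loss, and no figure for R² is given. Patients on SSRIs or SNRIs for less than 2 months are excluded, which makes a large stratum-by-time effect less obvious, though it does not rule one out. Where the error exists, it is conservative and leaves the estimate unbiased.

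A reader might also put the loss at 126 × R²/(1 − R²), about 7 or 14 patients for R² of 0.05 or 0.10. That measures the width of the interval. Stratified allocation has already reduced the true variance, so the loss of power is the smaller 4 or 9 patients, and power without the stratum does not fall below the planned level.

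Finally, a reader might say that the pooled effect speaks to neither use. It does not follow. The pooled effect is a valid average over a mixed population. The hypotheses in General objectives do not mention antidepressant status, the sample size is for one pooled comparison, and the aim can be read as describing who is eligible. The remark in the abstract is conditional and concerns implementation. What survives is narrower: an average alone does not establish efficacy for each use.

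**Conclusion.** The point holds in a limited, conditional form. Randomisation is stratified by antidepressant use, and the stated primary model does not include it. If antidepressant use explains 5% or 10% of the HADRS-17 variance left after baseline, the model's SE is 2.6% or 5.4% too wide, alpha is 0.044 or 0.039 instead of 0.050, and 1.4 or 2.7 percentage points of power are given up. If it explains nothing, there is no loss. These results rest on assumed values of R², blocks formed within strata, and an effect of 0.5 SD.

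On interpretation, the planned analysis estimates the average over stand-alone and add-on use. Separate statements for each would need estimates by stratum, and 126 patients cannot give these with confirmatory precision.

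**What to change.** - Add antidepressant use (AD+ / AD-) and its interaction with time to the primary and secondary repeated-measures models. Leave the arm-by-stratum term out of the primary model, so that the primary result stays the pooled effect.
- Stratify the response odds ratios by antidepressant use.
- Report the arm difference in each stratum and the arm-by-stratum interaction with 95% CIs, labelled descriptive because of the power shown above.
- Word the conclusions so that efficacy is not claimed for stand-alone and add-on use separately from the pooled result alone.

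The stratum is already recorded at randomisation. The cost is one two-level factor with its time interaction and one supportive table, with no change to sample size or conduct. The change should be made before unblinding.
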